Nine-month isoniazid (INH) monotherapy (9H) is a standard TPT regimen recommended by the WHO. However, its effectiveness is limited by poor treatment complicance, partly owing to the long duration of the regimen. WHO recommended a 3-month regimen of weekly rifapentine (RFT) and INH (3HP) as an alternative ^[5]^. However, the safety profile of 3HP in Chinese population raises concerns ^[6]^.

Due to the high clinical heterogeneity, complex disease conditions and medications in RDs patents, the high-quality studies on TPT in this population is very limited. Considering the high risk of ADRs due to existed organ damage and concomitant medication which is almost inevitable in RDs patients, TPT regimens should be selected with caution. Based on previous studies and clinical experience from our center, we modified the 3HP regimen to 3HP-PUMCH, which involves twice weekly RFT at 450mg and daily INH at a maximum dose of 300mg for 3 months. We evaluated the efficacy, safety and completion of 3HP-PUMCH compared to the standard 9H regimen in high-risk RDs patients with LTBI.

1. **Objectives**
   1. To determine the non-inferiority of the 3HP-PUMCH regimen compared to the standard 9H regimen in preventing ATB in high-risk RDs patients with LTBI.
   2. To compare the safety profile and treatment completion rates between the two regimens.
2. **Methods**
   1. **Study design**

The study is a multi-center, open-label, non-inferiority, randomized controlled trial.

- 1. **Study population**
     1. Eligible criteria

1. Aged 18-70 years;
2. Diagnosed with at least one of the high-risk RDs including systemic lupus erythematosus (SLE), Takayasu's arteritis (TA), Behcet's disease (BD), primary Sjogren's syndrome (SS), rheumatoid arthritis (RA) and ankylosing spondylitis (AS);
3. Not currently using biologics;
4. Taking any of the following medications: ①≥15mg daily of prednisone or equivalent; ②at least one of the following immunosuppressive agents: methotrexate (MTX), cyclophosphamide (CTX), mycophenolate mofetil (MMF), cyclosporine A (CsA), azathioprine (AZA), tacrolimus (FK-506), leflunomide, iguratimod and tripterygium wilfordii; ③initiating TNF inhibitors treatment.
5. Positive for blood T-SPOT.TB (≥24 SFCs/10^6^ PBMC).
   - 1. Exclusion criteria:
6. Suspected or confirmed ATB,
7. Seropositive status for HIV-Ab,
8. Seropositive status for HCV-Ab or HBV surface antigen,
9. Severe liver damage (total bilirubin > 3mg/dL or aminotransferase > 2ULN) or liver cirrhosis,

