10. Prior use of TPT,
11. History of allergy to INH or RFT,
12. Pregnancy or lactation.
    1. **Randomization**

Participants were randomly allocated in a 1:1 ratio into the 9H and 3HP-PUMCH groups using a computer-generated random sequence. Randomization was stratified in the research center. A random sequence was generated using a fixed-block randomization method with a block length of 4. Allocation concealment was maintained using a web-based central randomization system.

- 1. **Interventions**
     1. Experimental Group

3HP-PUMCH regimen: INH once daily, 5 mg/kg (with a maximum daily dose of 300 mg), combined with RFT twice a week, 450 mg each time, for 3 months.

- - 1. Control Group

9H regimen: INH once daily, 5 mg/kg (with a maximum daily dose of 300 mg), for 9 months.

- - 1. Concomitant Treatment

RDs Treatment: The patient's baseline RDs treatment was followed according to the best available clinical guidelines/consensus and adjusted as needed by the treating clinician. A uniform RD treatment regimen was not stipulated.

- 1. **Outcomes**
     1. **Primary outcomes**

The occurrence of ATB up to the end of the follow-up period (24 months after randomization).

1. Diagnosis criteria:

- Microbiologically confirmed ATB: Biological specimens were positive by smear microscopy, culture, Xpert MTB/RIF, or other molecular biological diagnostic methods.
- Clinically diagnosed ATB: A clinical diagnosis of ATB was made when patients present characteristic symptoms (e.g., fever, cough, chest pain, night sweats, weight loss), supported by highly suggestive laboratory and imaging findings. Additionally, the diagnosis must be corroborated by a positive response to empiric TB treatment.

1. Diagnosis Adjudication:

All suspected ATB cases were reviewed by an external Endpoint Event Adjudication Committee (comprising two TB and one rheumatology experts) who were blinded to the TPT regimen allocation.

- - 1. **Secondary outcomes**

1. Permanent discontinuation of TPT due to serious adverse events (SAEs) or ATB occurrence.
2. ADRs related to prophylactic drugs (assessed by WHO-UMC causality criteria).
3. Completion rate of TPT.

Completion of treatment are defined as the consumption of at least 22 doses of RFT and at least 81 doses of INH within 16 weeks for the 3HP-PUMCH group, and 243 doses of INH within 52 weeks for the 9H group.

- 1. **Data collection and follow up**
     1. **Data collection:**

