1. Baseline Risk Assumptions: The 2-year incidence of ATB in the 9H group is approximately 3.6% (annual incidence of 1.8%). This estimate is based on cohort studies conducted in high TB burden countries/regions^[7]^, with a focus on populations at high risk for TB, such as those receiving high-dose glucocorticoids or immunosuppressive treatment, or planning to receive iTNF. The study inclusion criteria clearly define this high-risk subgroup, rather than evaluating all patients with RDs in general. While no study has specifically included RD patients with these risk factors, the incidence estimate in this study is derived from available data in high-risk populations.
2. Non-Inferiority Margin (Δ): The pre-set margin is 1.4% (absolute risk difference). This margin is determined based on the clinically acceptable increase in risk (i.e., the maximum additional risk allowed for 3HP-PUMCH relative to 9H).
3. Expected Effect and Sample Size Limitation: The expected incidence in the 3HP-PUMCH group is 1.1% (with an expected risk difference of -2.5%). This hypothesis is informed by similar studies in the HIV population, which observed 1.01% vs 3.50% cumulative TB rates, yielding a risk difference of −2.49% in favour of 3HP^[8]^. While standard non-inferiority designs typically assume a 0% risk difference, this study incorporates this assumption based on the higher adherence and better protective effects of the short-course regimen containing rifapentine in clinical practice, as well as the expected reduction in toxicity with the modified regimen. This design reflects a practical clinical approach under conditions of limited resources and a lack of sufficient evidence. We acknowledge that this assumption might result in a sample size that may not meet statistical power requirements under a 0% risk difference assumption, which is one of the limitations of this study.
4. Statistical Power: 80% statistical power, one-sided alpha level of 0.025.
5. Sample Size Calculation: 236 participants per group.
6. Total Sample Size (Accounting for Attrition): Assuming a 10% attrition rate, a total of 526 eligible participants will be enrolled.
   - 1. **Analysis Sets**
7. Primary Analysis Set (mITT): The Modified Intention-to-Treat (mITT) analysis set includes all participants who were randomized and received at least one dose of the intervention drug.

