8. Sensitivity Analysis Set (PP): The Per-Protocol (PP) analysis set includes all participants from the mITT set who completed the TPT.
   - 1. Statistical Methods
9. Primary Outcome Analysis

- The cumulative incidence and its 95% CI will be estimated using the Exact Method.
- Non-inferiority will be concluded by comparing the upper bound of the 95% CI for the difference in cumulative incidence with the pre-set non-inferiority margin (1.4%).
- Non-Inferiority Test Criteria: If the upper bound of the 95% CI is < 1.4%, non-inferiority will be considered demonstrated.
- Superiority Test: If non-inferiority is achieved, a further assessment will be made to determine whether the upper bound of the 95% CI is < 0.0% to test for superiority.

1. Secondary Outcome Analysis

Descriptive statistical methods will be used. The rates of adverse drug reactions (ADR), liver toxicity, and other outcomes will be compared using chi-square tests, and 95% CIs will be calculated.

1. Sensitivity Analysis

In the mITT population, incidence rates per person-year will be calculated, and the difference in incidence rates and its 95% CI will be estimated.

1. Software

Analysis will be conducted using R software (version 4.4.1).

1. **Monitoring and Oversight**

The trial is overseen by a Coordinating Center (Peking Union Medical College Hospital). An external Endpoint Event Adjudication Committee is established to independently review and validate all primary outcome events (ATB), ensuring objectivity and consistency.

1. **Ethics and Dissemination**
   1. **Research Ethics Approval**

This study received approval from the Ethics Committees of the participating hospitals (Approval Number: JS-1498). All procedures comply with the ethical standards of the institutional and national research committees and with the Helsinki declaration.

- 1. **Informed Consent**

All participants provided written informed consent prior to enrollment in the study.

- 1. **Protocol Amendments**

Any substantial changes to the protocol will be submitted to the Ethics Committees for approval and will be updated in the trial registry (ChiCTR).

- 1. **Dissemination Policy**

The results of this study will be published in peer-reviewed journals (such as this manuscript) and presented at scientific conferences. The final protocol will be accessible to readers as supporting information accompanying the main manuscript. All authors meet the criteria for authorship.

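### Every planned efficacy analysis in this open-label trial excludes randomized participants who took no dose, so none keeps the full randomized comparison; the direction and size of any bias are unknown

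*Protocol*

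**What the plan says.** Section 3.1 (Study design) states: "The study is a multi-center, open-label, non-inferiority, randomized controlled trial". Under section 3.3 (Randomization), "Participants were randomly allocated in a 1:1 ratio into the 9H and 3HP-PUMCH groups".

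Section 3.7 (Analysis Sets) names two sets. The primary one, mITT, "includes all participants who were randomized and received at least one dose of the intervention drug". The other, PP, is nested in it: the "analysis set includes all participants from the mITT set who completed the TPT". The Sensitivity Analysis paragraph stays in the same population: "In the mITT population, incidence rates per person-year will be calculated".

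Section 3.5 (Outcomes) defines the primary outcome as "The occurrence of ATB up to the end of the follow-up period (24 months after randomization"), so the clock starts at randomization and not at the first dose. Non-inferiority (upper 95% bound below 1.4 points) and, if met, superiority (upper bound below zero) are read from the interval for the difference in cumulative incidence.

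"Completion rate of TPT" is a secondary outcome, and comparing completion between the regimens is part of the second objective in section 2. Section 3.5 defines completion by doses taken. Section 3.7 names no analysis set for it or for any other secondary outcome.

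**The concern.** Randomization makes the arms comparable as assigned. A set that requires a first dose adds a condition met or missed after assignment. In a blinded trial that condition can seldom depend on the arm. Here participant and clinician know whether the course lasts 3 or 9 months before the first dose is taken, and the protocol describes no safeguard such as giving that dose at randomization. Concealed allocation protects the assignment and blinded adjudication protects the event classification; neither protects entry into the analysis set.

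The Background section gives reasons why uptake might differ in either direction: poor compliance with the long 9H course, and concern about the safety of 3HP in Chinese patients. If uptake does differ, the non-inferiority and superiority conclusions would rest on groups partly formed by choice, and no planned analysis would show how much that matters. Completion is exposed more directly, because someone who never starts is by definition a non-completer.

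**Working it through.** **1. The plan's own sample size.** Inputs from section 3.7: 3.6% in 9H, 1.1% in 3HP-PUMCH, margin 1.4 points, one-sided alpha 0.025, power 80%, attrition 10%.

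n = (1.960 + 0.842)² × [0.011×0.989 + 0.036×0.964] / (0.014 + 0.025)² = 7.849 × 0.045583 / 0.001521 = 235.2, so 236 per arm. Then 236/0.90 = 262.2, so 263 per arm and 526 in total. The stated figures reproduce. This point concerns the analysis set only.

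**2. Expected events.** 263 × 0.011 = 2.9 in 3HP-PUMCH and 263 × 0.036 = 9.5 in 9H, or about 3 versus 9.

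**3. Effect on the risk difference (RD).** Let f be the share of an arm that never starts and r the 2-year ATB risk in those people. The all-randomized risk is (1−f) × risk in starters + f × r. The protocol gives neither f nor r; the values below are assumptions, with r = 7.2% being twice the 9H rate.

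*Refusal mainly in 9H.* Risk in starters is set at the margin (5.0% vs 3.6%, RD 1.40), with f = 1% in 3HP-PUMCH and r = 7.2%. The 3HP-PUMCH risk is 0.99×5.0 + 0.01×7.2 = 5.022.

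| f in 9H | 9H risk, all randomized | RD, dosed set | RD, all randomized | 9H events dropped |
|---|---|---|---|---|
| 5% | 0.95×3.6 + 0.05×7.2 = 3.78 | 1.40 | 1.24 | 263×0.05×0.072 = 0.95 |
| 10% | 0.90×3.6 + 0.10×7.2 = 3.96 | 1.40 | 1.06 | 263×0.10×0.072 = 1.89 |

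About 0.2 events are dropped from 3HP-PUMCH (263×0.01×0.072 = 0.19). Here the dosed set gives the larger RD and is conservative for 3HP-PUMCH.

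*Balanced refusal of 2% in each arm, r = 7.2%.* 5.044 − 3.672 = 1.37, a shift of 0.03 points.

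*Refusal only in 3HP-PUMCH.* With the design rates (1.1% in starters), the all-randomized RD exceeds the dosed-set RD by f × (r − 1.1%).

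| f in 3HP-PUMCH | r = 3.6% | r = 7.2% |
|---|---|---|
| 2% | 0.05 points | 0.12 points |
| 5% | 0.13 points | 0.31 points |
| 10% | 0.25 points | 0.61 points |

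Here the dosed set favours 3HP-PUMCH.

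**4. Sensitivity to one event.** Upper 95% bounds with 263 per arm, in points. Wald and Newcombe intervals are used for illustration.

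| Events, 3HP-PUMCH vs 9H | Wald | Newcombe | Reading |
|---|---|---|---|
| 2 vs 9 | −0.23 | −0.12 | superiority met |
| 3 vs 9 | +0.26 | +0.41 | superiority not met |
| 4 vs 8 | 1.03 | 1.24 | non-inferiority met |
| 5 vs 8 | 1.51 | 1.75 | non-inferiority not met |

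These are borderline tables chosen to show fragility; they are not predictions. Removing the never-starter from the denominator as well (2/262 or 4/262) moves these bounds by only 0.01.

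**5. Completion.** If the dosed set is the denominator, completion is overstated by 1/(1−f): 1/0.95 = 1.05 at 5% and 1/0.90 = 1.11 at 10%. For example, an assumed 85% among starters is 85 × 0.95 = 80.8% or 85 × 0.90 = 76.5% of those randomized.

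**The case against.** The strongest reply is that the most obvious mechanism, refusal because 9H is long, makes the dosed set stricter for 3HP-PUMCH (1.40 against 1.24-1.06), while the all-randomized analysis would make non-inferiority easier to show. That is correct. A reader might infer that the exclusion invalidates the superiority test or tilts the trial towards the new regimen; the documents support neither. A bias in favour of 3HP-PUMCH needs refusals concentrated in that arm, which is possible but not documented.

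The mechanism is also an inference. Poor compliance with a long course most naturally means not finishing it. Both arms begin with the same daily isoniazid dose, and consent came before enrollment, so non-initiation may be rare. Even the assumed shifts of 0.16-0.34 points are small beside a standard error of √[(0.05×0.95 + 0.036×0.964)/263] = 1.77 points. All of this stands and limits the severity.

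A further objection is that untreated people in both arms pull the difference towards zero, which is the wrong direction for a non-inferiority claim (1.40 to 1.37 with 2% in each arm). This also stands, and it argues against simply replacing the dosed set for non-inferiority. The stated PP set offers no counterweight, because it is restricted to completers.

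Finally, a reader might infer that the protocol removes never-starters from the completion denominator. It does not say so. Of the two defined sets only mITT could serve, since every PP member completed by definition, but another denominator may be specified elsewhere.

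None of these replies explains why no all-randomized analysis is planned at all.

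**Conclusion.** The point holds in a limited form. The protocol itself fixes the primary and supporting sets, all of them exclude never-starters, and first-dose uptake occurs with the arm known. The full randomized comparison is therefore never reported.

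The direction and size of any bias cannot be settled from the protocol. Under the assumptions shown, refusal mainly in 9H makes the dosed set conservative for 3HP-PUMCH by 0.16-0.34 points, refusal only in 3HP-PUMCH favours that arm by 0.05-0.61 points, and rare or balanced refusal has a negligible effect. The margin is 1.4 points. The practical weight comes from the small event count: in borderline results a single excluded event can change the superiority or non-inferiority conclusion. The completion overstatement of 1/(1−f) is conditional on mITT being the denominator. The sample size is unaffected. This should be changed, but it does not by itself undermine the trial.

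**What to change.** In section 3.7, define a set of all randomized participants analysed by assigned arm, whether or not they took a dose. Then:

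- use it for the superiority test and for the completion rate, counting never-starters as non-completers;
- require it as a co-analysis beside mITT for non-inferiority, and state that both will be reported and how a disagreement will be interpreted;
- follow never-starters for ATB to month 24 at the month 6, 12, 18 and 24 visits already in section 3.6;
- report the number of never-starters and their reasons by arm;
- keep the dosed set for safety.

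The cost is wording plus follow-up of what is probably a small number of people. Parts of the protocol are written in the past tense, so some never-starters may be harder to trace; if so, report how many have unknown ATB status by arm. The statistical downside is slight dilution of the difference in the all-randomized analysis, which is why mITT stays beside it for non-inferiority. The sample size need not change on this account.

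### The per-protocol set keeps only completers of preventive treatment, so it drops on-treatment tuberculosis cases over a longer window in 9H than in 3HP-PUMCH and biases that supportive check against 3HP-PUMCH

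*Protocol*

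**What the plan says.** Protocol section 3.7 (Analysis Sets) makes mITT the primary set and gives a per-protocol set for sensitivity: "The Per-Protocol (PP) analysis set includes all participants from the mITT set who completed the TPT".

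Section 3.5 (Secondary outcomes) defines completion separately by arm:
- 3HP-PUMCH: "at least 22 doses of RFT and at least 81 doses of INH within 16 weeks for the 3HP-PUMCH group".
- 9H: "243 doses of INH within 52 weeks for the 9H group".

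The planned durations in section 3.4 are 3 and 9 months. The primary outcome in section 3.5 is ATB from randomisation to month 24 in both arms. The secondary outcomes in the same section include "Permanent discontinuation of TPT due to serious adverse events (SAEs) or ATB occurrence", so the protocol itself treats ATB as a cause of stopping preventive treatment for good. No exception keeps such a participant in the per-protocol set.

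**The concern.** Membership of the per-protocol set depends on something that happens after randomisation and that the primary event itself prevents. Someone diagnosed with ATB before the qualifying dose cannot complete, and leaves the set together with the event. If the two regimens had the same length, this would lower both risks about equally. Here one regimen is three times as long as the other, so more 9H events are lost than 3HP-PUMCH events.

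The set then compares roughly 15 months of residual risk in 9H with 21 months in 3HP-PUMCH as though both were 24-month risks. The difference is displaced from zero even when the regimens protect equally well. If this set missed the margin, nobody could tell a real weakness of the short regimen from the way the set was built.

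**Working it through.** **Inputs.** From section 3.7: 9H two-year risk 3.6%, 3HP-PUMCH 1.1%, margin 1.4 points, one-sided alpha 0.025, power 80%, 236 per group, 10% attrition, 526 in total. From sections 3.4 and 3.5: durations of 9 and 3 months; completion at 243 or 81 isoniazid doses; outer limits of 52 and 16 weeks; endpoint at 24 months. Assumption: constant hazard, varied in step 4, because the protocol gives no timing of ATB.

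**1. The plan's own figure.** n = (1.96 + 0.8416)² × (0.036 × 0.964 + 0.011 × 0.989) / (0.014 + 0.025)² = 235.2, so 236 per group. 236 / 0.9 = 262.2, so 263 per group and 526 in total. Both figures reproduce.

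**2. True equality at 3.6%, windows of 9 and 3 months.**
- Hazard: -ln(1 - 0.036) / 2 = 0.01833 per year.
- 9H, 15 months left: 1 - exp(-0.01833 × 1.25) = 2.27%.
- 3HP-PUMCH, 21 months left: 1 - exp(-0.01833 × 1.75) = 3.16%.
- Per-protocol difference: +0.89 points, or 64% of the margin, when the true difference is 0.
- In cases per 236: 236 × 0.036 = 8.5 expected in each arm. About 8.5 × 9/24 = 3.2 are dropped in 9H and 8.5 × 3/24 = 1.1 in 3HP-PUMCH.

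**3. Completion as a dose count.** With a dose every day, 243 and 81 doses are reached at 243/30.44 = 8.0 and 81/30.44 = 2.7 months. The risks become 2.42% and 3.21%, a difference of +0.79.

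**4. Range, changing one input at a time from step 2.** For an on-treatment hazard f times the later hazard, with the 24-month risk held at 3.6%, the later monthly hazard is -ln(0.964) / (24 - t + f·t), where t is the treatment time in months.

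| Change | 9H | 3HP-PUMCH | Difference (points) |
|---|---|---|---|
| f = 0.25 | 3.14% | 3.48% | +0.34 |
| f = 0.5 | 2.78% | 3.36% | +0.58 |
| f = 2 | 1.65% | 2.81% | +1.16 |
| Everyone takes the full 52 or 16 weeks | 1.82% | 3.06% | +1.23 |
| Both arms at 1.1% | 0.69% | 0.96% | +0.27 |

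Stacking the assumptions widens this to about +0.09 (1.1% risk, dose-days, f = 0.25) and +1.44 (3.6% risk, full windows, f = 2).

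**5. The planned effect, 3.6% versus 1.1%, windows of 9 and 3 months.**
- The 3HP-PUMCH hazard is -ln(0.989) / 2 = 0.00553 per year, so its per-protocol risk is 1 - exp(-0.00553 × 1.75) = 0.96%.
- The difference is 0.96 - 2.27 = -1.30 points instead of -2.50. On dose-days it is -1.44.
- The chance of meeting the margin with 236 per group (unpooled normal approximation) falls from 80% to about 65%: (0.014 + 0.0130) / 0.01159 - 1.96 = 0.37. This is before other non-completers are removed.

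**6. What a simple repair leaves behind.** Suppose ATB cases adherent up to diagnosis are retained while non-cases must still complete. Assume equal 3.6% risk, constant dropout, and completion of 70% in 9H and 90% in 3HP-PUMCH.
- 9H: on-treatment cases 1.149%, completers 69.04%, later cases 1.564%. Risk = (1.149 + 1.564) / (1.149 + 69.04) = 3.87%.
- 3HP-PUMCH: 0.434%, 89.59% and 2.828%. Risk = (0.434 + 2.828) / (0.434 + 89.59) = 3.62%.
- Difference: -0.24 points, now in favour of 3HP-PUMCH.

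**The case against.** The case for leaving this alone is substantial, and much of it stands.

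- **The primary decision does not use this set.** Non-inferiority rests on one comparison of the upper 95% confidence bound with 1.4%, and mITT is the primary set. A reader might infer that the claim depends on mITT and per-protocol agreeing. That is a common convention, but the protocol sets no such rule.
- **The direction is conservative.** More 9H events are removed, so this mechanism cannot produce a false finding of non-inferiority. Selection through non-completion for other reasons is a separate matter and is not quantified here.
- **The size depends on an assumption.** If ATB is rarer during treatment the bias shrinks, and it vanishes if none occurs then. The 64% figure is one scenario.
- **Completion is a dose count.** A reader might infer that completers are certain to be free of ATB for 9 and 3 months. The text does not support that: ATB after the qualifying dose is kept, and the 52- and 16-week limits are extremes.
- **There is no contradiction over sensitivity analyses.** A reader might see one, because the Sensitivity Analysis paragraph says "In the mITT population, incidence rates per person-year will be calculated" and does not mention the per-protocol set. A person-time analysis in mITT and a per-protocol set can coexist. The per-protocol analysis is simply not spelled out there, which a statistical analysis plan may do.

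None of this removes the mechanism, which follows from the definitions the protocol itself fixes.

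**Conclusion.** The point holds as a flaw in a supportive analysis. On-treatment ATB cases are excluded because of the primary event, over about 8 to 9 months in 9H and about 3 months in 3HP-PUMCH. With equal true risk of 3.6% and a constant hazard, the artefact is about +0.8 to +0.9 points against 3HP-PUMCH. It ranges from about +0.3 to +1.2 when on-treatment hazard, completion time or event rate is varied singly, against a margin of 1.4 points. Under the planned rates, nearly half of the expected advantage disappears from this set.

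The result assumes that ATB before the qualifying dose always ends preventive treatment, which the secondary outcome implies, and that some ATB occurs on treatment. The primary mITT conclusion is not at risk. The definition is worth correcting because a check that is off zero under equality cannot confirm or question the main result, but it is not a defect that must hold up the trial.

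**What to change.** Reword the per-protocol definition in section 3.7:

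- Do not exclude anyone because of ATB. Keep participants who were adherent up to the earliest of ATB, death or the end of the regimen.
- Judge adherence pro rata against the protocol's own completion thresholds, separately for each drug. For isoniazid, 81/90 and 243/270 are both 90% (30-day months). For rifapentine, 22 doses are 92% of 24 (12 weeks) or 85% of 26 (13 weeks), so one common percentage does not fit and the denominator must be stated.
- Count events from randomisation to month 24, and repeat the primary comparison in this set with the same confidence interval and margin.
- Because non-cases must still complete, a small bias towards 3HP-PUMCH can remain (about -0.24 points at the assumed 70% versus 90% completion). Therefore also report a person-time version that censors each participant at the point of non-adherence, which assumes that such censoring is unrelated to ATB risk. Describe both as supportive.

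No extra participants are needed. The real cost is data: dose counts up to the event date are required. Section 3.6 names a self-reported adherence scale with high, medium and low categories, collected at visits up to three months apart during treatment, and describes no dated dose count.

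### The non-inferiority decision rests on an exact-method cumulative incidence in everyone dosed, which on its natural reading ignores incomplete 24-month follow-up although 10% attrition is planned

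*Protocol*

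**What the plan says.** Protocol section 3.5 defines the primary outcome as ATB within 24 months of randomisation. Section 3.7 then fixes the analysis:

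- **Estimator:** "The cumulative incidence and its 95% CI will be estimated using the Exact Method".
- **Decision rule:** "If the upper bound of the 95% CI is < 1.4%, non-inferiority will be considered demonstrated". The interval is for the difference in cumulative incidence. If non-inferiority is shown, superiority is assessed by comparing the upper limit with zero.
- **Primary set:** the mITT "analysis set includes all participants who were randomized and received at least one dose of the intervention drug". It carries no follow-up requirement.
- **Attrition:** "Assuming a 10% attrition rate, a total of 526 eligible participants will be enrolled".
- **Follow-up time:** it enters only as a sensitivity analysis: "In the mITT population, incidence rates per person-year will be calculated", with a rate difference and its 95% CI. No margin is given on that scale.

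The primary analysis names no censoring rule, no time-to-event estimator and no rule for participants lost before month 24.

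**The concern.** An exact interval for a proportion needs a numerator and a denominator and has no place for partial follow-up. With everyone dosed in the denominator, a participant who leaves at month 3 without recorded ATB contributes a non-event for the remaining 21 months. The sample size treats the same person as contributing nothing, because it divides by 0.9. The two parts of section 3.7 do not fit together.

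This matters because the trial tests non-inferiority on an absolute scale. If the new regimen is truly worse, unobserved events lower both risks and draw the difference towards zero, which makes a false claim more likely. If loss differs by arm, the arm that loses more has its risk understated more. The analysis that decides the claim would then partly measure retention.

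**Working it through.** **Inputs from protocol section 3.7.** 9H risk 3.6%, 3HP-PUMCH risk 1.1%, margin 1.4 points, one-sided alpha 0.025, power 80%, attrition 10%. Allocation is 1:1 (section 3.3).

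**Assumptions added here.** Constant hazard over 24 months; the timing of loss and its split by arm; a score (Miettinen-Nurminen) rule for the difference, since the protocol does not name the interval method for it.

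**The plan's own figure.** With unpooled variance and a distance to the margin of 1.4 + 2.5 = 3.9 points:

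n = (1.960 + 0.842)² × (0.011 × 0.989 + 0.036 × 0.964) / 0.039² = 235.2, so 236 per arm.

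236 / 0.9 = 262.2, so 263 per arm and 526 in total. Both stated figures reproduce.

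**Apparent risk when losses count as TB-free.** For true 24-month risk p, hazard h = −ln(1 − p)/2 per year, and a fraction L lost at t years:

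apparent risk = (1 − L) × p + L × (1 − exp(−h × t)).

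Example with 10% lost at month 3 (t = 0.25), true risks 5.0% and 3.6%:

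- 3HP-PUMCH: h = 0.02565; 0.9 × 5.0% + 0.1 × 0.64% = 4.56%.
- 9H: h = 0.01833; 0.9 × 3.6% + 0.1 × 0.46% = 3.29%.
- Apparent difference 1.28 points against a true 1.40.

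**Chance of declaring non-inferiority**, by full enumeration of the two binomial counts at 263 per arm:

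| True risks (3HP-PUMCH v 9H) | Loss 3HP-PUMCH / 9H | Time of loss | Apparent difference (points) | Chance of claim |
|---|---|---|---|---|
| 5.0% v 3.6% (at margin) | none | – | 1.40 | 2.37% |
| same | 10% / 10% | month 12 | 1.33 | 2.58% |
| same | 10% / 10% | month 3 | 1.28 | 2.77% |
| same | 15% / 5% | month 3 | 0.90 | 4.46% |
| same | 5% / 15% | month 3 | 1.65 | 1.65% |
| 1.1% v 3.6% (planned) | none | – | −2.50 | 84.3% |
| same | 10% / 10% | month 3 | −2.28 | 83.0% |

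In the rows at the margin, the last column is the false non-inferiority rate; in the rows at the planned effect it is power. Both unequal patterns average the planned 10%.

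**The margin on the rate scale.** With 3.6% control risk, a 1.4-point margin means 5.0%. The rates are −ln(0.95)/2 = 2.56 and −ln(0.964)/2 = 1.83 per 100 person-years, a difference of 0.73.

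**The case against.** - **The TB-free rule is not written down.** This stands. The mITT definition fixes who belongs to the set, not how a missing outcome is handled, and the division by 0.9 would suit a complete-case denominator. A rule could also sit in the SAP, which was not available. What remains is that the protocol itself fixes an exact method and an all-dosed set for the decision analysis. Dropping lost participants from the denominator would depart from that set.
- **The direction is not fixed.** This stands. A reader might infer that the plan favours non-inferiority whatever happens. It does so for equal loss when the new regimen is truly worse. At the planned benefit, equal loss moves the estimate towards the margin and costs about one point of power.
- **Greater loss in 3HP-PUMCH is not documented.** This also stands. A reader might infer it from that arm's shorter treatment, but section 3.7 expects better adherence with the short course. In section 3.6 both arms attend at months 6, 12, 18 and 24; 9H has one extra visit, at month 9. The reverse imbalance is conservative.
- **The person-year analysis already deals with follow-up time.** In part. It accounts for unequal follow-up, but it has no stated margin and does not drive the decision.
- **Kaplan-Meier has its own assumption.** True: it needs loss to be non-informative, so it does not remove bias when those lost differ in TB risk. Hence the further sensitivity analysis proposed below.

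**Conclusion.** The concern holds in a limited form. The decision analysis of a 24-month outcome, on its natural reading, takes no account of incomplete follow-up that the same section plans for.

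At the protocol's own 10% attrition, equal in both arms, the effect is small: the false non-inferiority rate rises by about 0.2 to 0.4 points (2.37% to 2.58% or 2.77%). It becomes material only if loss differs by arm, and then in either direction: 4.5% or 1.65% for a ten-point imbalance at month 3. These figures rest on the assumed constant hazard, timing and split of loss, and on the score rule.

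The documents do not support saying that the protocol instructs lost participants to be counted as TB-free, or that the analysis is biased towards non-inferiority in general. The change is worth making because a better estimator exists, works on the same margin and costs little.

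A separate, smaller point concerns superiority. The trial is open-label (section 3.1) and the mITT set drops anyone who never starts after learning the allocation. The protocol gives no number of such participants, so no size can be put on this.

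**What to change.** In section 3.7:

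1. Make the primary estimate the between-arm difference in 24-month risk by Kaplan-Meier, or by Aalen-Johansen with death as a competing event. Fix the choice in advance. Censor at the last contact at which TB status was established, and compare the upper 95% limit with the unchanged 1.4%.
2. Name an interval suited to few events, since only about 263 × (0.011 + 0.036) = 12 are expected. One option is a hybrid (MOVER) interval built from arm-specific limits; a Wald interval is not suitable.
3. Keep the crude exact proportion as a supportive analysis, and say how participants without a month-24 status are counted in it.
4. State the converted margin for the person-year analysis: about 0.73 per 100 person-years, given 3.6% control risk and a constant hazard.
5. Add a sensitivity analysis in which TB risk after loss differs by arm, and report the amount and timing of loss in each arm.
6. Separately, run the superiority test on all randomised participants.

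The sample size calculation stays as it is. The cost is protocol wording, modest programming and a slightly wider interval when follow-up is incomplete. The follow-up visits needed are already scheduled in section 3.6.
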